| 1. **Limitations of the study design, data sources, and analytic methods**   The aim of this study is to make inferences about the effect of antibiotic treatment overall, and in different patient groups in order to develop models to support antibiotic prescribing decisions in primary care. The major challenge is to adjust for confounding by disease severity, i.e. the fact that patients with more severe infections are more likely to be prescribed an antibiotic. Estimating disease severity in primary care is challenging because clinical measures such as vital signs are not well recorded. We have outlined methods to try and account for this issue including the use of instrumental variables and treatment propensity scores.  This study will be limited to some extent in the outcomes it will be able to investigate. First, as shown in I. Sample size considerations, the power needed to identify differences in treatment effects by co-comorbidities will be limited by sample sizes available for extremely rare outcomes. However, as we have chosen our outcomes based on their importance for patients requesting antibiotics, we will look at more common outcomes like re-consultation for which sample sizes should be sufficient. The final effect sizes that we will be powered to detect will then depend on the actual number of observations for respiratory, urinary and skin/soft tissue infections. We will take this a priori power into account when discussing our findings. Secondly, we will rely on the representativeness of the data sources from which we obtain our outcome measures. In particular, HES A&E data coverage is incomplete in comparison to national A&E attendances. We expect this to bias our results for A&E consultations towards the null, limiting our power to detect true differences in outcomes. Again, this limitation will be taken into consideration when discussing any findings on A&E admissions.  By relying on clinical codes to define exposure and measure outcomes, this study may be subject to misclassification. It is known that considerable inter-practice variation exists in coding certain conditions. GPs may not use diagnostic codes to define every episode of e.g. URTI. We will aim to mitigate misclassification of URTIs and other infections by building on comprehensive code lists from previously published studies using CPRD and THIN and reviewing them with experts in the field (see Appendix Table 2). Even so, code lists may not always accurately represent the real reasons why antibiotics were prescribed, as much of the clinical information that is obtained during the consultation is not captured in them. However, one of the main aims of this study is to get a better understanding of this problem through linkage of prescribing and indication. This is further aided by exploring differences in coding between practices will be explored with novel methods, as described in *O. Plan for addressing confounding*.  Although the prescription data recorded in CPRD is of high quality, prescription records themselves do not guarantee that individuals will necessarily take the antibiotics. CPRD data describes antibiotics prescribed and it’s known that patients do not fill 100% of their prescriptions. With no valid way to estimate the proportion of prescribed CPRD antibiotics that were dispensed, we will be unable to ascertain which patients were adherent to the prescribed medications. Furthermore, the antibiotic prescription data used in this work is based on those prescribed from primary care, and thus does not take into account antibiotics prescribed from alternative healthcare sources, such as online, walk-in centres, and urgent care. |
| 1. **Amendments**   **Adding additional covariates in line with previous literature**  Summary:  We would like to include the following additional covariates:   - - Coronary Heart Disease   - Stroke   - Heart Failure   - Peripheral Arterial Disease   - Liver disease   - Immunosuppression   - Composite (Charlson Comorbidity Index - CCI)   Reasoning:  We originally excluded cardiovascular co-morbidities, liver disease, immunosuppression and the CCI because of insufficient power to detect our main effects of interest, i.e. differences between co-morbidities in the number needed to treat (*N. Data/ Statistical Analysis*, step 4.). While this is still the case, we now believe that we do need to include these variables as covariates in our analysis in order to ensure unbiased results and comparability to results from previous literature1,16. In line with the original protocol, **no** attempt will be made to interpret their effect sizes with regards to the number needed to treat (steps 4.-5.), as sample size calculations have indicated low power.  **Additional analysis of confounding**  Summary:  Preliminary analysis has shown unexpected differences to previously published results. These differences could be due to differences in datasets used, differences in countries analysed, or differences in practices and patients included. We plan to further investigate the reasons for the observed difference to be able to present the findings in context.  Reasoning:  After performing analysis of steps 1. and 2. described in section *N.* Data/ Statistical Analysisand comparing them to previous studies on THIN, we found differences in reported rates of antibiotic prescribing and rates of incidence of infection. The size of these differences was up to 30% and persists even when identical code lists and procedures are used. We are not entirely clear why we see these differences, but they seem unlikely to be chance findings and may be clinically relevant, thus warranting further investigation. All previous studies were performed using UK-wide, primary care-only data. We speculate that differences arose because we limited our sample to England-only, HES-linked data. For example, a recent study suggested that i) there might be differences in antibiotic prescribing behaviour between UK countries, with England having lower rates of prescribing than its neighbours.16 These conclusions are in line with our findings, but alternative explanations exist: ii) there might be differences between practices that agree to link their data to HES and ONS as compared to those who don’t, iii) there might be differences between patients who opt out of linkage as compared to those who don’t, and finally iv) there might be differences in practices that contribute to THIN compared to those that contribute to CPRD. In order to be able to appropriately interpret and use the results of this study, we aim to investigate which of the above hypotheses is the most likely. We will rerun all analysis in steps 1. and 2. (which use only primary care) on all patients in CPRD, using the definitions in *K. Study population* but omitting criteria concerning data linkage (bullet points a., c. and the second half of d.). The results from these calculations will then be used to judge whether the observed differences are due to practices excluded because of their country (i), due to practices excluded because of linkage (ii), due to patients excluded because of linkage (iii), or due to practices which are not in CPRD at all (iv). |

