| 1. **Objectives, Specific Aims and Rationale**   *Objective*  To investigate the use of antibiotics and their protective effect against complications of infection to inform the development of risk prediction models to guide antibiotic treatment decisions for suspected infection in primary care.  *Aims*   1. Estimate the incidence of i) GP consultations for infection and ii) antibiotic prescriptions by: age-group, gender, SES, ethnicity, selected co-morbidities, obesity and smoking status 2. Describe antibiotic prescribing patterns linked to the reason for the prescription by: age-group, gender, SES, ethnicity, selected co-morbidities, obesity and smoking status 3. Estimate the incidence of adverse outcomes in the following 28 days including: hospital admission for infection; A&E admission; re-consultation for infection; re-consultation for antibiotic side-effects (rash, nausea, …) and death for patients with a GP consultation for i) respiratory tract infection ii) urinary tract iii) skin/soft tissue infection, comparing patients with each listed age/co-morbidity group (including smoking status and obesity) to non-comorbid patients 4. Estimate the number of patients needed to treat with antibiotics to avoid one infection-related adverse outcome, comparing the results for each age/co-morbidity group to non-comorbid patients 5. Develop risk prediction tools to support clinical decision making and communication with patients   *Rational*  We have previously shown that more than half of all antibiotic prescriptions in primary care are issued to less than 10% of patients, and that this 10% of patients have high levels of co-morbidity.1 Targeting such high-frequency users of antibiotics in antimicrobial stewardship programmes might provide opportunities for a more effective intervention approach. Underlying this hypothesis is the assumption that it might be safe and feasible to reduce prescribing in patients with the highest levels of antibiotic prescribing, many of whom have co-morbidity.  To investigate whether higher rates of antibiotic use are likely to be justified in higher risk patients compared to patients who lack these risk factors, we will undertake a series of studies to investigate which patients in terms of age, gender, SES, ethnicity, selected co-morbidities, obesity and smoking get the most antibiotics. We will determine which patients are most likely to receive antibiotics for which infections and relate this to national guidance on antibiotic prescribing. To estimate whether the protective effect of antibiotics differs according to the patient’s age and the presence of co-morbidity, obesity or their smoking status, we will estimate the risk of infection related adverse-outcomes, comparing patients who have been treated with antibiotics to those who have not been treated with antibiotics for each of these groups. We will use these estimates to calculate the number of patients who need to be treated with antibiotics to avoid one infection-related adverse outcome (NNT), accounting for age, gender, SES, ethnicity, co-morbidity, obesity and smoking status. This will inform the development and validation of individualised risk-prediction models to support clinical decision-making and patient communication around the need for antibiotic treatment for suspected infection in primary care. |

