| 1. **Study Background**   Over the past 70 years antibiotics have revolutionised how we practice medicine, underpinning routine surgery through to cancer therapies and organ transplantation. Unfortunately, most antibiotics have a finite lifespan as drug resistant strains emerge; an inevitable consequence of bacterial evolution.  Resistance to antibiotics is largely driven by the inappropriate use and overuse of these drugs in humans and animals. Although the majority of highly drug resistant infections emerge in hospitals, 75% of antibiotics for human use are prescribed in primary care.2 The most common reasons for prescription of an antibiotic in primary care are for the treatment of respiratory tract, urinary tract, and skin and soft tissue infections. Despite guidelines on the management of these infections,3 large variations exist in the rates of antibiotic prescribing between individual practices in the UK4–6, with some practices prescribing at twice the rate compared to other sites.  Significant efforts have been made to understand the factors that influence the GP’s decision to prescribe an antibiotic.7 Examples of interventions that have been developed to reduce antibiotic use include symptom-based scoring systems or point-of-care diagnostics to improve diagnostic certainty.8 There have also been a range of initiatives to improve communication between the doctor and patient, to reduce unnecessary antibiotic use.9 The main tool currently used in primary care is the Treat Antibiotics Responsibly Guidance Education Tools (TARGET) toolkit, which was designed by Public Health England.10 It aims to influence prescribers’ and patients’ personal attitudes, social norms and perceived barriers to optimal antibiotic use.  To date, these interventions have targeted all patients who consult for an infection in primary care, despite the fact that some patients are never or rarely prescribed antibiotics, whereas others may have many courses of antibiotics in a single year. This patient-level variation in antibiotic prescribing is likely to be driven by a combination of demographic, behavioural and clinical factors including the presence of co-morbidity. For example, higher rates of antibiotic prescribing might be justified in patients with COPD for the treatment of bacterial infective exacerbations.6 By contrast, for conditions such as obesity, where there is also evidence that patients are more likely to be prescribed antibiotics,1 the clinical indication for increased antibiotic use is less clear.  We speculate that reductions in antibiotic resistance may require targeted public health interventions aimed at reducing antibiotic prescribing for patients who have the highest frequency antibiotic use. To test whether it might be safe and feasible to reduce antibiotic prescribing to patients with co-morbidity in clinical practice (who account for a substantial burden of total antibiotic use), we estimate the protective effect of antibiotic treatment against infection-related adverse outcomes, comparing effects in patients with co-morbidity to those in controls without co-morbidity. Based on this, there is then a need to develop tools enabling a better understanding of risk to support clinical decisions about which patients need antibiotics and communication with patients. |

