| 1. **Study Type**   First we will **describe** the incidence of and relationships between antibiotic prescribing, GP consultation for infection and infection related adverse outcomes for all patients and for subgroups of patients based on risk factors including: age, gender, SES, co-morbidity, smoking status and obesity.  Next we will then **test the hypothesis** that the protective effect of antibiotics against adverse outcomes of infection differs between groups of patients with and without these risk factors.  Finally, we will use our results to inform the **methodological** development of risk prediction models to support clinical decisions around antibiotic treatment. |

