| 1. **Data/ Statistical Analysis**   *1. Estimate the incidence of i) GP consultations for infection and ii) antibiotic prescriptions*  For every patient in cohort 1, data on all consultations for infection and antibiotic prescriptions occurring within the study period will be extracted. We will estimate the incidence of GP consultations for infection and antibiotic prescriptions. This will be done for all consultations and prescriptions, and then separately for each category of infection and each class of antibiotics, based on chapter 5.1 of the British National Formulary (BNF) (see Appendix Tables 1 & 2). The denominator will be estimated as total person-time contributed by patients in the cohort during the study period. We will use Poisson regression to estimate the adjusted rate of consultation and prescription, taking account of the effect of age, gender, SES, ethnicity, selected co-morbidity, smoking and obesity. Random effects will be included to take account of clustering of observations by practice. Rates will be assessed for overdispersion by additionally fitting a negative binomial model and testing for alpha greater than zero via a likelihood-ratio test. If rates are found to be overdispersed, the negative binomial model will be used instead of a Poisson model. Adjusted rate ratios will be presented with 95%-confidence intervals.  *2. Describe antibiotic prescribing patterns linked to the reason for prescription*  The overall number of antibiotic prescribing episodes will be calculated for each patient individually, counting all recorded prescriptions between 1st April 2007 and 31st December 2015. For each episode, a clinical indication will be ascertained. Read codes for a diagnosis or symptom of infection recorded on the same day as the antibiotic prescription will be assumed to represent an indication for the prescription. Where more than one possible indication within the same type of infection is recorded on the day of prescription, the more granular code will be used. If multiple indications across different types of infection are recorded, the prescription will be labelled as having multiple indications. Conversely, if no infectious indication for a prescription was found, the prescription will be labelled as having no infectious indication and we will look for any non-infectious codes associated with the date of antibiotic prescription. The ten most common indications will be established and compared to the same numbers for the period from 1998-2001.14 This approach will be replicated for each class of antibiotics based on chapter 5.1 of the BNF. Patterns of repeat consultation or prescription during episodes of infection which may be prolonged will be investigated for each antibiotic prescription extracted in objective 1. We will define a new episode as a consultation or prescription recorded at least 28 days after any previous consultation for infection or antibiotic prescription. We will undertake sensitivity analyses to investigate the impact of using different time periods to define an episode. We will also examine the use of regular (prophylactic) antibiotic treatment.  Proportions and appropriate 95%-confidence intervals will be calculated and all results will be stratified by age-group, gender, SES, ethnicity, selected co-morbidity, obesity and smoking status. Descriptive data will be displayed graphically.  *3. Estimate the incidence of adverse outcomes in the following 28 days*  For each of the selected clinical infection syndromes in the nested cohort study, events in CPRD, HES and ONS will be searched for all adverse outcomes of interest (see *M.* Exposures, Health Outcomes§ and Covariates). Crude incidence rates of for each outcome will be calculated for patients who were treated (exposed) and not treated (unexposed) with an antibiotic. The denominator will be estimated as the total person-time contributed by patients at risk of each adverse outcome, taking account of the fact that this will be different for each outcome. For example, exposed and unexposed patients cannot consult General Practice if they have been admitted to hospital and should therefore not contribute to the denominator during this period when estimating rates of GP re-consultation in the 28 days following consultation for infection. A Poisson regression model will be used to estimate adjusted rates of adverse outcomes in each group, controlling for age, gender, socio-economic status, ethnicity, co-morbidity, obesity and smoking status and assessing for interaction between age and co-morbidity. Random effects will be included to take account of clustering of observations by practice. If the outcomes are overdispersed, negative binomial models will be used instead of Poisson models. Adjusted rate ratios will be presented with 95%-confidence intervals.  *4. Estimate the number of patients needed to treat with antibiotics to avoid one infection-related adverse outcome*  For each clinical infection syndrome-related adverse outcome identified in objective 3, the odds of that outcome in the 28 days following consultation for those treated with antibiotics (unexposed) and not treated with antibiotics (exposed) will be estimated using logistic regression. We will calculate adjusted odds ratios for the protective effect of antibiotics, adjusting for age, gender, SES, ethnicity, year/season, co-morbidity and the probability of receiving antibiotic treatment (see *O. Plan for addressing confounding*) and assessing for interactions with age and co-morbidity. We will use mixed models to adjust for clustering at a practice level and to take account of clustering of observations within a patient due to repeat episodes of infection. Where there is a significant effect of antibiotics between treated and untreated patients, the NNT or NNH to prevent one individual from developing an adverse outcome is calculated as *1/(absolute risk difference)*. A significant effect will be defined by a p-value < 0.05 for the coefficients of antibiotic treatment and its interactions. To avoid an arbitrary cut-off point, p-values close to 0.05 will also be assessed but discussed separately. The NNT will then be used to assess the clinical relevance of any significant differences found. Whilst the relative risk reduction (RRR) may be similar, the NNT may be different due to differing background risk. This will be explored.  *5. Develop risk prediction tools to support clinical decision making*  For each cohort (i.e. for each of the clinical syndromes of UTI, RTI and SSTI), we will develop a logistic regression risk model to predict the risk of adverse outcomes if patients are treated versus not treated with antibiotics. Models will be developed on a random sample of 80% of the observations within a cohort, reserving 20% of the data to estimate the model’s predictive performance.  A negative outcome will be defined as the occurrence of any of the following within 28 days following the index consultation: hospital admission for infection or complication; re-consultation for infection; A&E admission; death. Antibiotic treatment will be defined as a prescription of an antibiotic on the day of consultation for clinical syndrome. Risk factors will be selected based on the analyses outlined in objectives 1-4 and broadly grouped into: socio-demographic variables, co-morbidity and clinical presentation. Biologically plausible interactions between risk factors and age and between risk factors and co-morbidities will be examined.  Whereas age and sex will be forced into the model, other risk factors will be added in order of their significance in objective 4. Risk factors will be kept in the model if they improve the predictive performance of the model as defined by model discrimination and model calibration.17 For example, a risk factor will be used in the model if it improves discrimination and/or calibration. If a variable improves discrimination but reduces calibration, it will still be included in the model, but will be omitted if it increases calibration at the cost of discrimination.  Model discrimination, i.e. the model’s ability to correctly identify patients with and without an outcome, will be estimated using the concordance (c) statistic.18 The c statistic represents the probability that between two randomly chosen patients, one with the outcome and one without, the model assigns a higher score to the patient with the outcome. As a second measure, model calibration will be assessed using the Hosmer-Lemeshow test.18 We will additionally assess model calibration graphically for reasons for poor calibration by comparing the mean observed outcome in deciles of predicted risk. In this calibration plot, the intercept indicates the extent to which predictions are systematically too low or too high, while the slope reflects overfitting of the model.  For each model, we will estimate the internal validity of discrimination and calibration estimates using cross-validation with bootstrap subsampling based on 1000 iterations. In a secondary analysis, we will assess model performance in subgroups by age, sex and co-morbidity.  Finally, we will develop a simplified scoring system using the risk factors in the model,17 assigning the total score to a specific absolute risk of adverse outcomes in the 28 days following consultation, comparing outcomes if an individual is treated versus not treated with antibiotics. We will assess the predictive performance of the risk scores using the approaches outlined above. |

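### Step 4 ties the NNT and clinical relevance to p < 0.05, so a co-morbidity group with a non-significant result need get no absolute effect and no bound on the benefit forgone, although safety of reduced prescribing is the stated motive

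*Protocol*

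**What the plan says.** The Study Background introduces the comparison with "To test whether it might be safe and feasible to reduce antibiotic prescribing to patients with co-morbidity in clinical practice" and says how this will be done: "we estimate the protective effect of antibiotic treatment against infection-related adverse outcomes, comparing effects in patients with co-morbidity to those in controls without co-morbidity". The rationale under Objectives treats safety as a premise: "Underlying this hypothesis is the assumption that it might be safe and feasible to reduce prescribing in patients with the highest levels of antibiotic prescribing". The one formal hypothesis, under Study Type, is "that the protective effect of antibiotics against adverse outcomes of infection differs between groups of patients with and without these risk factors".

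Section N, step 4, sets the criterion: "A significant effect will be defined by a p-value < 0.05 for the coefficients of antibiotic treatment and its interactions". It then limits the absolute measure: "Where there is a significant effect of antibiotics between treated and untreated patients, the NNT or NNH" is obtained as the reciprocal of the absolute risk difference. Relevance follows the same route: "The NNT will then be used to assess the clinical relevance of any significant differences found". The cut-off is softened: "To avoid an arbitrary cut-off point, p-values close to 0.05 will also be assessed but discussed separately". Step 4 adds that NNTs may differ because background risks differ, and that this will be explored.

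Section O plans inverse probability weighting partly so that absolute risks and NNTs can be assessed in different groups. The limitations section says a priori power will be considered when findings are discussed. No passage says how large a loss of benefit a non-significant result would still allow, or how such a result is to be read.

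**The concern.** Whether prescribing can safely be reduced in a group depends on how much benefit would be given up there, and how much more than that the data cannot exclude. An absolute risk difference with its confidence interval answers this. Step 4 produces the absolute measure when a coefficient is significant and gives no undertaking to produce it otherwise. The groups with the least information are therefore the ones for which the reader is told least.

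The results feed risk models meant to support prescribing decisions. A bare non-significant interaction for a co-morbidity could be taken as meaning that these patients gain no more from antibiotics than others do, when the data may be compatible with a considerably larger gain.

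**Working it through.** **Inputs (section I).** 5% significance and 80% power; antibiotic effect ORAB = 0.69; outcome risk 2.4%; N = 3,355,353 respiratory, 1,342,141 skin/soft tissue and 671,070 urinary; smallest detectable effects in the respiratory cohort ORAB 0.975 and ORCO 0.83. ORCO is the interaction odds ratio and was derived for COPD.

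**Reproducing the plan's figures.** The Wald formula for logistic regression is N = (1.960 + 0.842)² × [1/(x·p1·q1) + 1/((1−x)·p0·q0)] / (ln OR)², where p0 and p1 are the untreated and treated risks, q = 1 − p, and x is the treated share. The text does not give x. With x = 0.80 (found by trial) and 2.4% as the untreated risk, the formula gives 16,511 against the stated 16,512. At 0.04% risk it gives 971,057, as stated. The detectable ORAB at 3,355,353 is 0.9753 against the stated 0.975. A two-sided 5% test is therefore the right reading. The interaction figure of 258,247 cannot be fully reproduced, because COPD prevalence and the assumed ORCO are not in the text, so I take the stated ORCO of 0.83 as given.

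**Standard error of ln ORCO.** Respiratory: |ln 0.83| / 2.802 = 0.1863 / 2.802 = 0.0665. For the other cohorts, multiply by sqrt(3,355,353 / N).

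**Chance of a non-significant result if the true ORCO is 0.83.** P ≈ Φ(1.960 − 0.1863/SE).

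| COPD | SE | 0.1863/SE | P(non-significant) | 95% CI if the estimate is 1: exp(±1.96·SE) |
|---|---|---|---|---|
| Respiratory | 0.0665 | 2.80 | 20% | 0.88 to 1.14 |
| Skin/soft tissue | 0.0665 × 1.581 = 0.1052 | 1.77 | 57% | 0.81 to 1.23 |
| Urinary | 0.0665 × 2.236 = 0.1487 | 1.25 | 76% | 0.75 to 1.34 |

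**What this means in events.** Treated odds = untreated odds × ORAB × ORCO. At 2.4% untreated risk:
- ORCO 1: treated risk 1.668%, so 7.3 events avoided per 1,000 treated (NNT 137).
- ORCO 0.83: combined OR 0.69 × 0.83 = 0.573, treated risk 1.389%, so 10.1 per 1,000 (NNT 99).
- ORCO 0.747, the lower limit in the urinary row: combined OR 0.515, treated risk 1.252%, so 11.5 per 1,000.

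A urinary estimate of exactly no interaction would thus leave room for 11.5 rather than 7.3 events avoided per 1,000, taking ORAB and background risk as fixed.

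**Background risk alone.** With ORCO = 1 but an assumed untreated risk of 4.8%, the treated risk is 3.362%: 14.4 events avoided per 1,000 (NNT 70). A null interaction on the odds scale does not show equal absolute benefit.

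**Other co-morbidities.** Section H counts 36,119 COPD, 79,056 CKD, 107,382 diabetes, 216,379 asthma and 358,930 obese patients. Let COPD prevalence π be 1% to 5% (assumed), and let each other prevalence π′ be π times the ratio of counts. Multiply the SE by sqrt[π(1−π) / (π′(1−π′))]. P(non-significant) at a true ORCO of 0.83 becomes:

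| | Skin/soft tissue | Urinary |
|---|---|---|
| CKD | 26–28% | 55–57% |
| Diabetes | 14–18% | 43–47% |
| Asthma | 1–4% | 15–25% |
| Obesity | 0–2% | 4–18% |

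**The case against.** The strongest reply is that this is an estimation study. The safety sentence is in the background and goes on to say that effects will be estimated; the numbered aims are worded as estimating, describing or developing; and the one formal hypothesis is that effects differ, which an interaction test fits. Weighting is planned with absolute risks by group in view, differing NNTs are to be explored, near-0.05 results are discussed, and power will inform interpretation. Details of intervals may also sit in an analysis plan that is not shown. All this is fair, and it rules out calling the whole design wrong. It does not remove the condition on significance, which the protocol itself sets and which works against the estimation aim.

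Three stronger readings are tempting and not supported:

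- **That the plan will treat non-significance as safety.** The protocol never says so. It leaves that reading open.
- **That a non-significant coefficient is the only result that could favour reduction.** A significant effect with a very large NNT, an NNH, or an interaction showing less protection in co-morbid patients could also do so.
- **That the rule also fails for trivial but significant effects.** An ORAB of 0.975 at 2.4% risk is 0.6 events per 1,000 (NNT about 1,700), and the planned NNT step would show exactly that.

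Nor do the documents make a non-inferiority margin obligatory. In a retrospective cohort with acknowledged residual confounding, a very large sample could clear a margin through bias.

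**Conclusion.** The point holds in limited form. The study is motivated by whether reducing antibiotics in co-morbid patients might be safe, yet step 4 provides the absolute effect and the relevance judgement only for significant results. Where the result is not significant, nothing in the plan bounds the benefit forgone.

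The gap matters most for COPD, where a true interaction of 0.83 would be missed about 20%, 57% and 76% of the time in respiratory, skin and urinary infections. CKD and diabetes in urinary infection are also affected materially; asthma and obesity much less so.

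These figures assume that the standard error scales with 1/sqrt(N), with the same outcome risk, treated share and co-morbidity prevalence in each cohort. They ignore clustering and weighting, which would normally lower power. Against that, the protocol calls 3,355,353 a minimum from only 162 practices, so the real cohorts may be larger. Outcomes rarer than 2.4% would do worse.

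**What to change.** In section N, step 4:

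1. Report the adjusted absolute risk difference (untreated minus treated) with its 95% CI for every co-morbidity group, syndrome and outcome, regardless of p-value. Also report the co-morbid versus non-co-morbid difference in risk difference with its CI.
2. State that a non-significant antibiotic or interaction coefficient is not evidence that reduced prescribing is safe.
3. State that any such conclusion will rest on the upper confidence limit of the benefit forgone. Add the caveat that residual confounding by indication, which section O says leads to underestimating protection and the limitations section calls the major challenge, biases that limit downward and so towards reassurance.
4. Keep the p < 0.05 interaction test for the Study Type hypothesis that effects differ.

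A pre-set margin for the largest acceptable loss is optional and for the investigators to decide; if used, it should be fixed before step 4 is run.

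The cost is a change of wording and longer results tables. No new data are needed, since the weighted analysis already planned can supply the estimates. The downside is that some groups, chiefly the rarer co-morbidities in urinary infection and the rarer outcomes, will be reported as inconclusive.
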